## Abstract

**Introduction:**

Over the last two decades, the use of opioids for the treatment of chronic pain in England has steadily increased despite lack of evidence of both long-term effectiveness in pain relief and significant, well-documented physical and mental adverse events. Guidelines recommend tapering when harms outweigh benefits, but the addictive nature of opioids hinders simple dose-reduction strategies. Improving the Well-being of people with Opioid Treated CHronic pain (I-WOTCH) trial tests a multicomponent self-management intervention aimed to help patients with chronic non-malignant pain taper opioid doses. This paper outlines the methods to be used for the economic analysis of the I-WOTCH intervention compared with the best usual care.

**Methods and analysis:**

Economic evaluation alongside the I-WOTCH study, prospectively designed to identify, measure and value key healthcare resource use and outcomes arising from the treatment strategies being compared. A within-trial cost-consequences analysis and a model-based long-term cost-effectiveness analysis will be conducted from the National Health Service and Personal Social Service perspective in England. The former will quantify key parameters to populate a Markov model designed to estimate the long-term cost and quality-adjusted life years of the I-WOTCH intervention against best usual care. Regression equations will be used to estimate parameters such as transition probabilities, utilities, and costs associated with the model’s states and events. Probabilistic sensitivity analysis will be used to assess the impact of parameter uncertainty onto the predicted costs and health outcomes, and the resulting value for money assessment of the I-WOTCH intervention.

**Ethics and dissemination:**

Full ethics approval was granted by Yorkshire & The Humber—South Yorkshire Research Ethics Committee on 13 September 2016 (16/YH/0325). Current protocol: V.1.7, date 31 July 2019. Findings will be disseminated in peer-reviewed journals, scientific conferences, newsletters and websites.

**Trial registration number:**

International Standard Randomised Controlled Trial Number (49 470 934); Pre-result.

Strengths and limitations of this studyFirst economic evaluation of a complex intervention Improving the Well-being of people with Opioid Treated CHronic pain (I-WOTCH) to support opioid tapering.The economic analyses use patient-level information to inform a de-novo decision model.I-WOTCH’s decision model will enable estimation of the costs, health consequences, and uncertainty associated with opioid use and tapering over a lifetime horizon.Valuable evidence for potential implementation of the self-management support intervention aimed at opioid tapering.Uncertainties may remain as to the long-term effectiveness and cost-effectiveness of the I-WOTCH intervention due to the limited follow-up duration of the current trial.

## Background

Nearly half of the UK adult population (43%) is living with chronic pain (ie, pain lasting >3 months), the prevalence of which increases with age.^1^ Opioids are commonly prescribed for chronic pain and a recent study reports an increase in the number of opioid prescriptions (approximately 34%) in England between 1998 and 2016.^2^ Analysis of prescription data shows that after this long increasing trend, there is a slight decrease in the annual number of opioid prescriptions for pain since 2016.^3^ Despite the demonstrated short-term effectiveness of opioids, evidence of their long-term impact in terms of pain relief and improvement in functional status is scant.^4 5^ This situation is compounded by concerns over the fact that long-term use of opioids can lead to adverse events (at an estimated absolute rate of 78% in trials using a placebo as a comparator) affecting the respiratory, cardiovascular, gastrointestinal and central nervous systems.^6^ These include common adverse events such as dry mouth, nausea and constipation, as well as more serious adverse events including sleep-disordered breathing, respiratory depression and opioid-related deaths (at an absolute rate of 7.5%).^6–8^ Equally concerning is the fact that opioid use is associated with mental health and anxiety disorders, major depression and dysthymia.^9^ Their long-term use may cause problematic patterns of substance use, leading to substance use disorders (ie, abuse and dependence).^10^ Risk factors for opioid-related adverse events include older age, higher doses of this class of drugs and their long-term use.^11 12^

Clinical guidelines for prescribing opioids in chronic pain recommend tapering when the possible harms from their use outweigh any expected benefits^13^ and yet, to our knowledge, no validated protocol or intervention exists to help patients reduce their opioid doses and manage their chronic pain.^14^ A number of studies have evaluated interventions (eg, acupuncture, ketamine-assisted dose reduction and behavioural strategies such as motivational interviewing, psychiatric consultation, cognitive behavioural therapy and mindfulness) that support opioid tapering.^15–18^ The conclusions drawn by these studies are limited by the quality of their design or insufficient follow-up period.^14^ Relevant for our study, there are no existing economic evaluations of opioid-tapering strategies in the management of chronic non-malignant pain.

Improving the Well-being of people with Opioid Treated CHronic pain (I-WOTCH) is a National Institute for Health Research-funded randomised controlled trial (RCT) evaluating the effectiveness and cost-effectiveness of a patient-centred, multicomponent self-management intervention targeting withdrawal of strong opioids among those living with chronic non-malignant pain.^19^ The I-WOTCH trial is designed to help people reduce their opioid consumption, manage pain interference and enhance their quality of life.

This paper describes the protocol for the economic analysis that has been designed as an integral part of the I-WOTCH trial.

## Methods

### Study details (population, setting, location, intervention and comparator)

A detailed study protocol for the I-WOTCH trial has been reported in a separate manuscript.^19^ Briefly, I-WOTCH is a multisite, patient-centred, open RCT enrolling adult patients with non-malignant chronic pain in England. The trial’s target sample size is 542 participants, individually randomised (1:1) to receive the I-WOTCH intervention or best usual care. The I-WOTCH intervention is an 8–10 weeks’ course—consisting of a mixture of group sessions led by two trained I-WOTCH facilitators, two one-to-one individual sessions and two telephone consultations with the I-WOTCH-trained nurse facilitator—adjunct to best usual care. Best usual care consists of general practitioner (GP) care with relaxation package and a booklet called ‘My Opioid Manager’.

### Planned start and end dates

The I-WOTCH study started in September 2016 and is expected to end in March 2021. The economic analysis is expected to begin in October 2020.

### Type of economic evaluation (cost-consequences and cost-effectiveness analyses)

Two types of economic analysis will be conducted: a within-trial cost-consequences analysis (CCA) and a long-term model-based cost-effectiveness analysis (CEA), the details of these are provided in the Analysis section.

### Study perspective

The perspective for both the CCA and CEA will be that of the National Health Service and Personal Social Service for England.

### Time horizon

The CCA and CEA will adopt a 12-month and a patients’ life time horizons, respectively.

### Discount rate

Estimates of mean cost and health benefits observed during the 12-month trial follow-up period will not be discounted (for the purpose of the CCA), while those predicted to accrue beyond the study follow-up (for the purpose of the CEA) will be discounted using a 3.5% annual discount rate as per National Institute for Health and Care Excellence (NICE) guidelines.^20^

### Identification, measurement and valuation of health outcomes

Table 1 describes the variables of interest to the economic analyses of I-WOTCH, the frequency of data collection and data sources.

**Table 1 T1:** Data collection strategy for I-WOTCH’s economic analyses

Data collected	Source	Time of collection
*Baseline data*		
Age	PtQ	Baseline
Gender	PtQ	Baseline
Ethnic group	PtQ	Baseline
Current work status	PtQ	Baseline
Age at leaving full time education	PtQ	Baseline
Pain duration	PtQ	Baseline
Opioid intake duration	PtQ	Baseline
Pain conditions	PtQ GPRs	Baseline At 12 months only
Pain severity stratification group	PtQ	Baseline
*Measures of health benefit*		
Activities of daily living (PROMIS-PI-SF-8A)	PtQ	Baseline, 4, 8 and 12 months
Severity of opioid withdrawal symptoms (ShOWS)	PtQ PtD	Baseline, 4, 8 and 12 months Weekly over first 4 months
Generic health-related quality of life (EQ-5D-5L)	PtQ PtD	Baseline, 4, 8 and 12 months Weekly over first 4 months
*Resource use (volume, admissions, consultations, attendances and/or contacts)*		
Medications	PtQ GPRs	Baseline, 4, 8 and 12 months At 12 months only
Hospital	PtQ GPRs	Baseline, 4, 8 and 12 months At 12 months only
Hospital outpatient	PtQ GPRs	Baseline, 4, 8 and 12 months At 12 months only
GP surgery	PtQ GPRs	Baseline, 4, 8 and 12 months At 12 months only
GP home	PtQ GPRs	Baseline, 4, 8 and 12 months At 12 months only
GP telephone	GPRs	At 12 months only
Practice nurse	PtQ GPRs	Baseline, 4, 8 and 12 months At 12 months only
Practice nurse telephone	GPRs	At 12 months only
District nurse (ie, at home)	PtQ GPRs	Baseline, 4, 8 and 12 months At 12 months only
NHS 111	GPRs	At 12 months only
Occupational therapist	PtQ	Baseline, 4, 8 and 12 months
Counsellor	PtQ	Baseline, 4, 8 and 12 months
Psychologist	PtQ	Baseline, 4, 8 and 12 months
Social worker	PtQ	Baseline, 4, 8 and 12 months
Physiotherapist	PtQ	Baseline, 4, 8 and 12 months
Referrals	GPRs	At 12 months only
Investigations	GPRs	At 12 months only
Ambulance incidents	GPRs	At 12 months only
Accident and emergency	GPRs	At 12 months only
Other	PtQ GPRs	Baseline, 4, 8 and 12 months At 12 months only

EQ-5D-5L, 5-level EQ-5D version; GP, general practitioner; GPRs, GP records; I-WOTCH, Well-being of people with Opioid Treated CHronic pain; NHS, National Health Service; PROMIS-PI-SF-8A, Patient-Reported Outcomes Measurement Information System pain interference-short form-8A; PtD, patient diary; PtQ, patient questionnaire; ShOWS, Short Opiate Withdrawal Scale.

The CCA will consider the following three health outcome measures over the 12-month trial follow-up period:

*Activities of Daily Living* (ADL)—measured using the Patient Reported Outcomes Measurement Information System pain intensity short form-8A questionnaire (PROMIS-PI-SF-8A).^21^

*Severity of opioid withdrawal symptoms*—measured using the Short Opiate Withdrawal Scale (ShOWS).^22^
The *5-level EQ-5D* version (EQ-5D-5L) instrument—a preference-based generic measure of health-related quality of life typically used in healthcare economic evaluation.^23 24^

The PROMIS-PI-SF-8A comprises eight questions rated on a scale of 1–5 that aim to measure the degree of interference of pain on day-to-day activities, work around the home, ability to participate in social activities, household chores, fun activities, enjoyment of social activities, enjoyment of life and family life. The total raw score is the sum of individual responses to each question thus forming a maximum score of 40 and a minimum score of 8. Higher scores reflect large interference or change in participant’s ability to perform daily activities. This instrument supports calculation of a common metric and will be converted to a T score.^21^

ShOWS identifies the severity of opiate withdrawal symptoms on 10 different categories namely: feeling sick, stomach cramps, muscle spasms, feeling of coldness, heart pounding, muscular tension, aches and pains, yawning, runny eyes and insomnia. The response to each question is attributed to an individual score of 0–3, with 0 indicating no symptoms, 1 mild, 2 moderate and 3 severe.^22^ Higher overall scores (estimated as the sum of all individual scores with a maximum score of 30 and a minimum score of 0) indicate higher severity of opioid-withdrawal symptoms.

The EQ-5D-5L Questionnaire^23^ describes health in five domains (mobility, self-care, usual activities, pain or discomfort, and anxiety or depression). Each domain has five levels of severity (1—no problems/2—slight problems/3—moderate problems/4—severe problems/5—unable to do). A response consists of a sequence of five digits, for example, 12315, 12112, which represent the level of severity on each domain reported by the respondent. Combinations of the levels of the five domains describe 3125 possible health states. Several valuation studies have been carried out in the literature to estimate value sets for a given country/region. These studies used methods consistent with economic theory to elicit the respondent’s preferences towards the health states defined by the EQ-5D. A value set to calculate utility values for the EQ-5D-5L has been published recently^25^ but is still subject to methodological controversy. Until the controversies are resolved, we will convert EQ-5D-5L responses onto the EQ-5D-3L scale using the mapping function developed by van Hout *et al*
26 following current NICE’s recommendation.^24^

The CEA will integrate predicted survival and EQ-5D index scores (for each model state and clinical event) to derive an estimate of quality-adjusted life years (QALYs)—the health benefit of choice in our CEA—under the I-WOTCH and best usual care strategies.

### Identification, measurement and valuation of resource use

As described in table 1, patient-level resource use data are collected in the trial and will be complemented by information routinely collected in GP records. Costing will be carried out in UK pound sterling at 2019 prices. Unit cost for tests, investigations, inpatient hospital admissions and day care procedures will be estimated using National Reference Costs and Healthcare Resource Group codes.^27^ Referrals and consultations will be costed using Personal and Social Services Research Unit (PSSRU) statistics.^28^ If necessary, we will use unit costs from previous versions of the PSSRU report^29 30^ and inflate them to the year 2019 using inflation and price indices from the Office of National Statistics (ONS).^31^ Costs associated with usual care will include the cost of the relaxation CD (ie, printing and production costs) and ‘My Opioid Manager’.

#### Microcosting of I-WOTCH intervention

A microcosting of the resources required to provide the I-WOTCH intervention will be conducted. A detailed description of the categories of resource use to be considered, their associated unit costs and the data collection forms used in the I-WOTCH microcosting exercise is provided in the online supplemental tables A1‒4. Salary, facility and travel costs will be assumed to be independent of the number of participants. Salaries for the facilitators and trainers will be estimated based on average daily salary by grade. The facility costs will be calculated based on the number of venues hired, number of days hired and daily venue hire rate. Travel costs will be considered as fixed cost per mile. Unit costs for nurses’ time for face-to-face and telephone consultations will be extracted from the PSSRU 2019.^28^ A per participant, locality and course cost of I-WOTCH intervention will be reported.

10.1136/bmjopen-2020-037243.supp1Supplementary data

#### Cost of medication

Unit costs of the medications (table 1) will be obtained from the British National Formulary (BNF).^32^ For each strength and preparation of a given pain killer drug, we will extract the cost per pack (or bottle) from the BNF and we will calculate the relevant morphine equivalent dose (MED) using the same algorithm used in the I-WOTCH clinical analysis. This is being updated from that used to estimate MED for stratification at the time of randomisation. For each opioid-based medication reported to have been used by individuals in the I-WOTCH study, we will estimate their unit cost per MED and use it to estimate a weighted average cost per MED over all opioid medications used in the trial.

#### Modelling

A Markov state-transition model was developed to facilitate the estimation of the long-term mean costs and QALYs associated with the I-WOTCH intervention and usual care. The initial conceptual structure of the model was informed by a systematic analysis of the components of the I-WOTCH intervention. This task was supported and enhanced by critically appraising published decision models that evaluated the use of opioids in chronic non-malignant pain. The face validity of the model structure was further refined by holding a series of meetings with the project team involving clinical experts from the I-WOTCH study. This process is described in detail in a separate related manuscript currently in preparation.

Figure 1 depicts a schematic representation of our final model structure, which is organised around five key states (ie, represented as ovals in figure 1). At any time period, patients can be in one of the following mutually exclusive states: (a) long-term opioid therapy (LTOT)—representing individuals candidate for the intervention, who have been using strong opioids for more than 3 months; (b) I-WOTCH tapering (IT)—individuals committed to tapering as part of the I-WOTCH intervention; (c) patient-driven tapering (PT)—individuals self-committed to tapering without the intervention; (d) successful opioid-less management of pain (SOLMP)—individuals completed withdrawal from opioid use; and (e) dead (D).

**Figure 1 F1:**
[figure not shown]
Simplified model structure showing patient flow during the I-WOTCH trial. At any time, individuals will be allocated to any five health states (shown as ovals). Individuals start in the long-term opioid therapy (LTOT) health state. Depending on the trial arm, they will move to either I-WOTCH tapering (IT) or patient-driven tapering (PT). The transition from LTOT to IT occurs only at the start of the trial and patients cannot go back to IT once they withdraw from it. Patients who have tapered their opioid doses completely will be in the successful opioid-less management of pain (SOLMP) health state. Patients may withdraw from IT or PT to move to LTOT health state. Similarly, patients in SOLMP may move to LTOT if they restart their opioid doses. The arrows‘ spearheads indicate the direction of allowed transition from one state to the other. Dead (D) state is an absorbing state where no transitions from the D state are allowed.

Each state is associated with an average cost and utility score, derived using the methods described in the Statistical analysis section. Spearheads of arrows in figure 1 represent the directions of allowed transitions per cycle. LTOT is the starting state for all patients in the I-WOTCH trial. Individuals in LTOT can engage with IT only once but are able to initiate PT at their will. While they remain in the LTOT state, individuals can experience opioid-related transient/emergent adverse events or persistent/serious adverse events. Occasionally, adverse events may trigger a transition from LTOT to PT. Individuals in IT or PT may withdraw from opioid tapering at any point in time and go back to LTOT. Individuals in IT or PT can transit to SOLMP state only when they are no longer taking any opioids. Finally, individuals are at risk of death at any point in time (ie, transitions into the absorbing D state are allowed from the LTOT, IT, PT and SOLMP states). A paper providing a detailed description of the conceptualisation of the model, health states definition, clinical events and associated transitions is in preparation. To maximise the use of the data collected during the trial and to model the events and transitions observed during the treatment and follow-up period, the state transition model uses a weekly cycle length during the first 4 months and monthly cycles beyond that.

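### The lifetime model, as described, has no place for a sustained partial opioid reduction, and names opioid adverse events explicitly only in the long-term opioid therapy state

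*Protocol article*

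**What the plan says.** The Modelling section presents its final structure, "which is organised around five key states": LTOT, IT, PT, SOLMP and dead. LTOT is introduced as candidates for the intervention "who have been using strong opioids for more than 3 months". The text with Figure 1 then sets these rules:

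- Entry to success: "Individuals in IT or PT can transit to SOLMP state only when they are no longer taking any opioids".
- Leaving a taper early: "Individuals in IT or PT may withdraw from opioid tapering at any point in time and go back to LTOT".
- Values: "Each state is associated with an average cost and utility score".
- Adverse events: "While they remain in the LTOT state, individuals can experience opioid-related transient/emergent adverse events or persistent/serious adverse events".

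Table 2 takes IT, PT and SOLMP utilities from patients' own EQ-5D. LTOT utility combines the literature with patient EQ-5D. PT cost includes self-reported and GP-record resource use as well as usual care; IT cost lists only the cost of the intervention. Death from every state uses ONS all-cause mortality. The Statistical analysis section names opioid use among the baseline predictors, and Subgroup analysis runs the model for patient profiles, with baseline morphine equivalent dose (MED) bands among the subgroups.

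On purpose and risk, the Background says: "The I-WOTCH trial is designed to help people reduce their opioid consumption" and "Risk factors for opioid-related adverse events include older age, higher doses of this class of drugs and their long-term use". The Strengths section says that the model reflects long-term adverse events of opioid use and of opioid withdrawal.

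**The concern.** The trial seeks lower consumption, and the article says that risk rises with dose. Yet the model's only success state is complete cessation. If many patients in the intervention arm settle at a lower dose without stopping, the lifetime analysis has no described way to carry that gain forward once they leave tapering. It would also miss the associated saving in opioid cost, although the Cost of medication section plans a cost per MED.

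The adverse-event description is a second gap. Patients in IT and PT can still be taking opioids, but neither state has explicit opioid adverse events, and withdrawal events are given no place in the state description. The gap is larger for IT, whose listed cost contains no patient resource use, and IT is reached only through the intervention. The two gaps can push the cost-effectiveness result in opposite directions.

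**Working it through.** The article gives no figure to reproduce, so the main check follows a patient through the stated rules.

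**A patient who cuts the dose and then holds it**

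1. SOLMP is closed, because opioids are still taken.
2. While still counted as tapering, the patient is in IT or PT, with that state's own cost and utility. Table 2 models remaining in each, but the text does not say when a patient on a stable lower dose stops counting as tapering. IT corresponds to a course of 8–10 weeks and is costed as the intervention alone, so a lifetime stay there would carry no opioid or other healthcare cost.
3. On leaving the taper, the patient enters LTOT, which is not split by dose.
4. Could a covariate restore the credit? The predictors in Statistical analysis and the MED bands in Subgroup analysis are baseline values. As an example, a patient who enters at 120 mg and settles at 40 mg has cut the dose by (120 − 40)/120 = 67%, but is still predicted from 120 mg.
5. Could mortality restore it? No: every state uses the same ONS source.
6. Could drug cost restore it? The weighted cost per MED is not linked to any state.

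So no credit for the sustained reduction is described after return to LTOT.

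**Adverse events in patients still taking opioids**

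| State | Events described | Quality-of-life effect | Cost effect |
|---|---|---|---|
| LTOT | Yes | Literature and patient EQ-5D | Literature, patient and GP-record resource use |
| PT | Not stated | Partly, through patient EQ-5D | Partly, through patient and GP-record resource use |
| IT | Not stated | Partly, through patient EQ-5D | Intervention cost only |

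**Illustration of scale, with assumed inputs**

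Omitted QALYs per randomised patient = p × u × D(T), where:

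- p is the between-arm difference in the share with a lasting partial reduction, assumed 0.10 to 0.40;
- u is the utility gain, assumed 0.01 to 0.05;
- T is further life, assumed 10 to 30 years;
- D(T) is the sum over months i = 0 to 12T − 1 of (1/12)/1.035^((i + 0.5)/12), using the 3.5% rate from the Discount rate section.

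D(10) = 8.46, D(20) = 14.46 and D(30) = 18.71. At £20,000 per QALY, the lower end of the NICE range in Incremental analysis:

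- Low: 0.10 × 0.01 × 8.46 = 0.008 QALY, about £170.
- Middle: 0.20 × 0.03 × 14.46 = 0.087 QALY, about £1,700.
- High: 0.40 × 0.05 × 18.71 = 0.374 QALY, about £7,500.

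This supposes that the model gives lasting partial reducers no gain at all, so it is an upper reading of that one omission. It does not include the opposing effect of the IT gaps.

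**The case against.** The strongest reply is that this is a condensed account. Figure 1 is captioned as simplified, and a separate paper on states, events and transitions is in preparation. Dose-dependence within a state, or explicit events in IT and PT, may appear there. That is fair, and it limits the point to the model as described. It does not remove the point, because the state rules, covariates and Table 2 sources are stated here and conflict with the article's own account of aim and risk.

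Four stronger readings are tempting, and the document does not support them:

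- *Any partial reduction counts as no change.* This holds only after return to LTOT. IT and PT have their own costs and utilities.
- *Patients in IT and PT have zero adverse-event risk.* The text places events in LTOT but sets no zero rate elsewhere, and observed EQ-5D and PT resource use already absorb part of their effect.
- *State values ignore dose altogether.* Baseline opioid use is a listed predictor. It is the later change in dose that goes unused. Partial reducers' data may also enter the LTOT average, which would spread their gain over all LTOT patients rather than discard it. Whether that average is pooled across arms is not stated.
- *The states leave out patients on weak opioids only.* The strong-opioid wording describes candidates for the intervention, and the Figure 1 caption returns anyone who restarts opioids to LTOT without a condition on strength or duration. The label is loose at most.

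**Conclusion.** The point holds in limited form. As described, the lifetime model has no state or dose level for a sustained lower dose. A patient who stops tapering short of zero is valued in LTOT like a patient with the same baseline profile who never reduced. Explicit opioid adverse events are confined to LTOT, and IT has no listed patient resource use. These features need reconciling with the Background and Strengths statements.

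The net direction of bias is unknown. Leaving out partial reduction would understate the benefit if the intervention produces more of it; leaving out explicit events and patient resource use in IT would favour the intervention. The size cannot be derived from the article: the 0.008 to 0.374 QALY range rests wholly on assumed inputs, and shows only that the first omission could matter to the cost-effectiveness ratio. The conclusion also assumes that the deferred model paper adds no dose-dependence within states.

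**What to change.** 1. Split LTOT into reduced-dose and unreduced-dose states, or let its cost, utility and adverse-event inputs depend on MED at the end of tapering. Table 1 already collects medication data by questionnaire at baseline, 4, 8 and 12 months and from GP records at 12 months.
2. State an assumption about how long the lower dose persists beyond 12 months, and vary it in scenario analysis.
3. Allow opioid adverse events in IT and PT. Where the state utility comes from observed EQ-5D, do not subtract the same loss again.
4. Include patient resource use in the IT cost, as is done for PT.
5. Say when a patient on a stable lower dose stops counting as tapering.

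The cost is a few more parameters, imprecisely estimated from 12 months of follow-up and carried through the probabilistic sensitivity analysis, plus one extrapolation assumption. MED updated throughout the lifetime horizon would be a larger step than one extra covariate, because it needs a projected dose path that the trial data do not supply. Fixing the dose when tapering ends avoids most of that burden.
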